### Participant enrolment and selection criteria

We collaborate with local doctors, nurses, and medical staff. The pregnant women are enrolled during their first antenatal care (ANC) visits (any trimester) by obstetricians and gynaecologists in the collaborating units. Written informed consent is obtained from the women after enrolment.

The inclusion criteria are as follows: (1) pregnant women who planned to deliver in the collaborating hospital; (2) singleton foetus; and (3) women agreeing to completing at least 2 years of postnatal follow-up. The exclusion criteria are as follows: (1) planning to move out of the town; (2) rejecting or not adhering to the 2-year follow-up; (3) participating in other research projects; and (4) chronic disease or chronic medication use (diagnosed pre-pregnancy). As a result, we will enrol term and preterm infants of any gestation, including neonates who require intensive care, and the medical records will be carefully collected.

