Probiotics are commonly used in paediatrics and even within families to regulate gut function. Probiotics are commonly defined as “live microorganisms which, when administered in adequate amounts, confer a health benefit to the host” [25]. The Food and Agriculture Organization/World Health Organization (FAO/WHO) consultation indicated that the potential health benefit is dose-based, however, the “adequate amount” in the definition is required to assess human interventions especially in early life periods. Although encouraging, existing conclusions are preliminary without longitudinal verification, and the reasoning behind using probiotics to deal with antibiotic resistance needs more evidence [26, 27].

Improper use of antibiotics and/or probiotics contributes to the development of antibiotic resistance. The strong influence of the infant resistome is mainly through the gut, oral cavity, vagina, and breastmilk, which enrich ARGs [28]. Additionally, some probiotic strains already have natural or mutant antibiotic resistance, and consumption may help restore gut microbiota imbalance caused by antibiotic treatment; however, some specific ARGs can be transmitted vertically, e.g., maternal microbial reservoir transmission during the vaginal delivery period to the infants. Moreover, strains could transfer antibiotic resistance to pathogenic microorganisms and other gastrointestinal commensal microorganisms through horizontal transmission [29]. Combining probiotics with antibiotics can reduce the incidence and severity of antibiotic-associated diarrhoea (AAD), so some special probiotics that do not carry resistance genes are selected to treat or prevent antibiotic side-effects [30]. However, the influence of vertically and horizontally transmitted aberrant microbiota on infants needs more evidence.

To address these issues, the Pregnancy and Birth Cohort in Northwest China (PBCC) was established to (a) clarify the association among antibiotic and probiotic exposure in early life, the microecology of the gut microbiota, and the development of antibiotic resistance; (b) investigate the long-term impact of antibiotics and probiotics on the health outcomes (including birth outcome, physical and cognitive development, disease and immune response) of infants and young children; and (c) provide a theoretical basis for the rational use of antibiotics and probiotics from a life course perspective.

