### Sample size calculation

From the perspective of antibiotic and probiotic use in early life, we considered using probiotics to prevent antibiotic-associated diarrhoea (AAD) in infants to calculate the sample size. The rate of AAD after broad-spectrum antibiotic treatment is reported to be 25%-53% in children [32]. A meta-analysis of probiotic uses to prevent AAD and *Clostridium difficile* infection among hospitalized patients revealed a statistically significant reduction in the risks of AAD (RR = 0.61, 95% CI 0.47 to 0.79) and a lower number of CDI at the end (RR = 0.37, 95% CI 0.22 to 0.61) [33].

Therefore, with a statistical power of 90% (β = 0.1) and a two-tailed significance level of 5% (α = 0.05), for each district, the sample size was calculated using the following formula:$$n=\frac{{{(z}_{\alpha }\sqrt{2\overline{p }\overline{q}}\pm {z }_{\beta }\sqrt{{p}_{0}{q}_{0}+{p}_{1}{q}_{1}})}^{2}}{{({p}_{1}-{p}_{0})}^{2}}$$$$p_1=RR\;\cdot\;p_0$$$$\overline{p }=\frac{1}{2}({p}_{0}+{p}_{1})$$

*where p*_*0*_ denotes the risk of AAD in the control group, *p*_*1*_ denotes the risk of AAD in the treatment group, and $$\overline{q }$$=1-$$\overline{p }$$.

Then, we estimated 354 as the minimum number of participants for each group (AAD or no AAD). Considering a 15% foetus attrition rate and 5% loss to follow-up rate, we expanded the number by 20%. Hence, for the three districts, we need to enrol 2,550 participants. Finally, after discussion with the site managers, 3,000 eligible women and their healthy, singleton infants will be recruited for this study.

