#### Pregnancy (including three trimesters)

During pregnancy (see T1-T3 in Fig. 1), the data will be collected from the ANC visits of the women. Several questionnaires will be carried out face-to-face in the first, second, and third trimesters of pregnancy to assess sociodemographic data, gestational age, environmental exposures, dietary patterns, nutritional supplements, psychological conditions, and medical and drug history, especially antibiotic and probiotic use. After the questionnaire investigation, body composition measurements, including body weight, fat percentage, fat mass, fat-free mass (FFM), muscle mass, total body water (TBW), TBW percentage, bone mass, basal metabolic rate (BMR), visceral fat and body mass index (BMI), will be conducted at the project office by using a body composition analyser (DC-430MA, TANITA Co. Ltd) for pregnant women.

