#### Outcomes of interest: Birth outcomes and early health outcomes

Birth outcomes include gestational age at delivery (weeks), mode of delivery (vaginal delivery or C-section), gender, infant Apgar scores, infant anthropometric measurements, and medications. The adverse birth outcomes are as follows [37]:A low Apgar score is defined as an Apgar score at 5 min of < 7.Low birth weight is defined as a live birth weighing < 2500 g.Small for gestational age infant (SGA) is defined as birthweight < 10% of that for a specific gestational age.Preterm birth is defined as a neonate born before 37 completed weeks.

The secondary health outcomes include antibiotic resistance, disease and treatments, physical development, and cognitive development, and they are recorded at every timepoint.Antibiotic resistance: It is reported that antibiotic resistance genes were found in infant faecal samples regardless of antibiotic exposure. In the study, we use 16S rRNA microbiome high-throughput sequencing and qPCR of ARGs for antibiotic resistance gene analysis.Disease and treatment: Common diseases in children often occur in the respiratory, digestive, or urinary systems, and the medical treatment and drug history are extracted from the HIS in the hospital.Physical development: Anthropometric measurements including weight (kg), height (cm), head circumference (cm), chest circumference (cm), and mid-upper arm circumference (cm), are standardized using WHO norms [37, 38].Cognitive development is assessed by standard Bayley Scales of Infant and Toddler Development (Bayley-IV), which is a widely used, comprehensive assessment of development for infants and toddlers aged 1 to 42 months [39] administered by trained research assistants.

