### Data management and statistical analysis

Data will be collected and managed using REDCap (Research Electronic Data Capture) tools by investigators, and questionnaire data entry will be conducted as soon as possible at each timepoint. Moreover, the external data including the records from the HIS, will be inputted regularly. All pregnant women enrolled in the study will be included in the final analysis.

The characteristics of the women or infants are described as the means ± SDs or medians for quantitative variables and percentages with numbers for categorical variables. One-way ANOVA is used to test the difference in means for continuous variables, and chi-square tests or Fisher’s exact test are used to summarize the associations of categorical variables.

To analyse the 16S rRNA gene sequence data, we will not only perform cross-sectional comparisons across individuals at the same time but also perform longitudinal follow-up within the same individual at different time points. All the data will be analysed using QIIME tools. (1) For community diversity and dissimilarity, alpha-diversity metrics including diversity (Shannon, Simpson) and richness (Chao, ACE) are used to measure diversity within species, and beta-diversity metrics are employed using the Bray‒Curtis or binary Jaccard distance matrix to measure the differential abundance among species based on antibiotic exposure, probiotic consumption, delivery mode and feeding patterns. (2) Then, principal coordinate analysis (PCoA), nonmetric multidimensional scaling (NMDS), the unweighted pair-group method with arithmetic means (UPGMA) and heatmap of species clusters are used to conduct cluster and dimensionality reduction. (3) Furthermore, linear discriminant analysis (LDA) effect size (LEfSe), and Metastats methods are used to identify significant differences from the phylum to genus levels among groups. (4) Multivariable analysis is used to adjust for confounding factors and analyse the associations between clinical and microbiota data and identify the influencing factors of abundance and diversity of the mother-infant microbiota. (5) For longitudinal data analysis of gut microbiota changes over the first two years, a linear mixed effects model or multilevel mixed effects model are used. (6) A Dirichlet multinomial mixtures (DMM) model [40] is used for gut microbiota community type determination.

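### No stated analysis of preterm birth allows for gestational age at entry or for exposure time; a crude comparison of any-use or third-trimester exposure would be biased towards protection

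*Protocol article*

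**What the plan says.** Under Participant enrolment and selection criteria the entry rule is "The pregnant women are enrolled during their first antenatal care (ANC) visits (any trimester) by obstetricians and gynaecologists", and later in that section "we will enrol term and preterm infants of any gestation, including neonates who require intensive care". The Background section gives as aim (b) to "investigate the long-term impact of antibiotics and probiotics on the health outcomes (including birth outcome, physical and cognitive development, disease and immune response". Under Outcomes of interest, "Preterm birth is defined as a neonate born before 37 completed weeks"; this is one of four adverse birth outcomes, listed ahead of the outcomes called secondary.

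The Data management and statistical analysis section keeps every enrolled woman in the final analysis. For categorical data it says that "chi-square tests or Fisher’s exact test are used to summarize the associations of categorical variables". The multivariable and mixed-effects models in that section are described for the 16S microbiota data, and the text that follows covers qPCR data. No analysis of birth outcomes is described separately.

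The raw material for a time-aligned analysis is collected. "Several questionnaires will be carried out face-to-face in the first, second, and third trimesters of pregnancy", and these cover gestational age and antibiotic and probiotic use. The section on independent variables adds that timing and duration of use are taken from the hospital information system. Foetal loss appears only under Sample size calculation: "Considering a 15% foetus attrition rate".

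**The concern.** Two separate problems arise when preterm birth is compared between exposure groups as a proportion.

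**Immortal time.** A woman who delivers at 33 weeks has seven fewer weeks in which to be prescribed, or asked about, a drug than one who delivers at 40. If the exposure window stays open until delivery, long pregnancies collect in the exposed group and short ones in the unexposed group.

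**Left truncation.** A woman enrolled at week 30 cannot contribute a preterm birth before week 30. One enrolled after 37 weeks cannot be a preterm case at all, yet the analysis set keeps her in the denominator.

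The study is meant to inform antibiotic and probiotic use by pregnant women. A spurious ratio well below 1 could be read as evidence of safety or benefit, and a spurious ratio above 1 as evidence of harm.

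**Working it through.** **The plan's own figure.** The article gives no figure for preterm birth. Its only computed sample size is for antibiotic-associated diarrhoea: p0 = 0.25, p1 = 0.61 × 0.25 = 0.1525, 90% power and two-sided 5% reproduce 354 per group. Then 354 × 1.2 = 424.8, rounded up to 425, and 425 × 2 × 3 = 2,550. Both match, but neither bears on this point.

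**Assumptions (not from the documents).**
- Gestational age at delivery: 93% Normal with mean 39.4 and SD 1.2 weeks, 7% Normal with mean 34.5 and SD 2.5, giving about 8.0% preterm.
- Exposure: constant rate of 0.0006, 0.005 or 0.02 per week. The lowest gives about 2% ever exposed, near the 2.1% prescription figure in the Background.
- Entry by trimester: 100/0/0, 60/30/10 or 34/33/33.
- True risk ratio: 1.

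**Hand check of immortal time.** For a rare exposure at a constant rate, the chance of being exposed is proportional to the length of the window. The crude ratio is therefore about RR = (mean window, preterm) / (mean window, all). Take 34.5 weeks for preterm births and 39.4 for term births.
- Any use, counted from conception: 34.5 / (0.92 × 39.4 + 0.08 × 34.5) = 34.5 / 39.0 = 0.88.
- Any use, counted from entry at week 10 on average: 24.5 / (0.92 × 29.4 + 0.08 × 24.5) = 24.5 / 29.0 = 0.84.
- Third-trimester use, from week 28: 6.5 / (0.92 × 11.4 + 0.08 × 6.5) = 6.5 / 11.0 = 0.59.

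**Simulation, 3 million pregnancies per scenario, no true effect.**

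| Exposure definition | Crude RR for preterm birth |
|---|---|
| Any use, all entry mixes | 0.80 to 0.89 |
| Any use, every woman enters in trimester 1 | 0.80 to 0.88 |
| Third-trimester use | 0.56 to 0.61 |
| First-trimester use, fully recorded | 0.98 to 1.00 |
| First-trimester use recorded only from entry, 60/30/10 | 0.99 to 1.06 |
| First-trimester use recorded only from entry, 34/33/33 | 1.08 to 1.17 |

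A second simulation, also at about 8% preterm, gave 0.81 to 0.90 for any use and 0.52 to 0.57 for third-trimester use. With exposure fixed before week 28, among women enrolled and still pregnant then, the ratio was about 1.0.

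**Left truncation.** The observed preterm proportion falls from 8.0% to 7.7% (60/30/10) or 7.0% (34/33/33). This also explains the ratios above 1. If first-trimester use is recorded only from entry, the exposed are all early entrants with risk 8.0%. The unexposed include the late entrants and sit near the overall risk: 8.0 / 7.0 = 1.14, or 8.0 / 7.7 = 1.04. The simulated values scatter around these because few women are exposed.

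**The case against.** The strongest reply is that the article never says birth outcomes will be compared by chi-square between ever- and never-exposed women. The test sentence is generic and sits in the paragraph on describing characteristics. Exposure timing and duration are recorded, and a fuller analysis plan, not shown here, may specify the time scale. This stands in part: the crude contrast is an inference, and the bias is conditional on it. But the article does fix the entry rule, the analysis set and the only test that fits a binary birth outcome, and together these do not suit preterm birth.

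A reader might go further and infer that entry in any trimester makes the drugs look protective. The documents and the check do not support that. The protective ratio appears even when every woman enters in the first trimester, so it comes from immortal time; left truncation alone only lowers the observed preterm risk. Nor is protection the general direction: it needs a window that stays open until delivery, disappears for a fully recorded first-trimester window, and can reverse if earlier use is missed. The drug histories and hospital records may reach back before enrolment, which would limit that reversal.

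A reader might also infer that foetal losses will be dropped from analysis. The article uses the 15% only to inflate the sample size and does not say so. Confounding by indication could shift the antibiotic estimate too, by an amount that the documents do not let one judge.

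**Conclusion.** The point holds as a conditional one that should be settled before birth outcomes are analysed. The stated test, applied to any use in pregnancy, would give a risk ratio of roughly 0.8 to 0.9 when the truth is 1; applied to third-trimester use, roughly 0.5 to 0.6. Late entry is a distinct problem of smaller size: about 0.3 to 1.0 percentage points off an 8.0% preterm risk, and early-exposure ratios of up to about 1.17 if use before enrolment is missed. These sizes rest on the assumed preterm rate, exposure rate and entry mix. The sign for windows open until delivery was the same in every scenario run. The documents do not establish that the study will report a protective bias; they leave the choice that decides it unstated.

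**What to change.** In Data management and statistical analysis, state that preterm birth and gestational age at delivery are not compared by crude chi-square but by one of two methods:

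1. A model on the gestational-age time scale (Cox or pooled logistic, followed to 37 weeks for preterm birth), with delayed entry at gestational age at enrolment and with antibiotic and probiotic exposure time-varying from its recorded date.
2. A landmark analysis: exposure fixed before a stated week, among women enrolled and still pregnant at that week.

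Define the exposure windows in advance, and say whether use before enrolment is recorded for late entrants. Report pregnancy losses after enrolment as an outcome and treat them as a competing event. The planning allowance implies up to 0.15 × 3,000 = 450, though it need not apply evenly to late entrants.

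The cost is analysis wording and a little more analysis work, since gestational age and exposure timing are already collected. The landmark version drops later entrants from that contrast: with a week-28 landmark, the third-trimester entrants, who are 10% or 33% of women in the two late-entry mixes assumed above.

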### Data collection

Data collection entails three stages including pregnancy, delivery and after birth, as shown by the timeline in Fig. 1. The ANC, delivery record, and follow-up data from the hospitals are independently managed by the hospital and collected by hospital staff using their routine hospital information system (HIS).

**Fig. 1 Fig1:**
[figure not shown]
Timeline of the Pregnancy and Birth Cohort in Northwest China (PBCC)

#### Pregnancy (including three trimesters)

During pregnancy (see T1-T3 in Fig. 1), the data will be collected from the ANC visits of the women. Several questionnaires will be carried out face-to-face in the first, second, and third trimesters of pregnancy to assess sociodemographic data, gestational age, environmental exposures, dietary patterns, nutritional supplements, psychological conditions, and medical and drug history, especially antibiotic and probiotic use. After the questionnaire investigation, body composition measurements, including body weight, fat percentage, fat mass, fat-free mass (FFM), muscle mass, total body water (TBW), TBW percentage, bone mass, basal metabolic rate (BMR), visceral fat and body mass index (BMI), will be conducted at the project office by using a body composition analyser (DC-430MA, TANITA Co. Ltd) for pregnant women.

#### Delivery/birth outcomes

After delivery, the delivery record and birth outcomes will be collected by the staff. The meconium will be collected within 3 days (T4 in Fig. 1); most of the meconium samples are the first faeces, and all samples are from the first three bowel movements.

#### After birth (follow-up)

During the afterbirth period, the follow-up time points are 42 days, 3 months, 6 months, 12 months, 18 months, and 24 months of age (T5-T10 in Fig. 1). The follow-up is designed to be embedded in the scheduled immunization and child health services, and therefore the data can be collected regularly in a timely manner. Specifically, the medication and prescription drug data will be obtained by the HIS, and the face-to-face questionnaire is used to collect information on caregivers, feeding patterns, nutritional supplements, and medical and drug history, especially antibiotic and probiotic use.

We also measure the physical development of children at every follow-up time point. We use uniform measurement tools including infant scales, electronic scales, and tape measures. After calibration, weight, height, head circumference, chest circumference, and mid-upper arm circumference are measured at least twice until reaching the minimum standard, and the average is recorded. Furthermore, offspring cognitive and behavioural health will be assessed by Bayley Scales of Infant and Toddler Development (Bayley-IV) at 12 and 24 months of age, which will be conducted by trained research assistants. Likewise, questionnaires on antibiotic knowledge and caregiver behaviours will be collected at these two time points.

### Biological sample collection and analysis

Faecal samples will be collected in three stages (shown in Table 1). The sample collection and laboratory experiments are as follows:

*Collection and preservation of samples for microbial testing*

We use a one-time sterile collection tube to collect fresh faecal samples with a 75% alcohol-disinfected stencil-sealed cover, which will be transferred quickly within two hours (using an icebox for temporary storage) to the hospital’s clinical laboratory and preserved in a -20 °C refrigerator and frozen after marking. Then, every two weeks, these samples will be temporarily transferred to a mobile fridge, with an average travel time of 60 min, ranging from 30 to 120 min to the lab located at Xi'an Jiaotong University, School of Public Health Centre. All the samples will be stored in a -80 °C refrigerator.

*DNA extraction and 16S rRNA gene amplicon sequencing*

Bacterial DNA is extracted from faecal samples with a QIAamp Fast DNA Stool Mini Kit (Qiagen, Cat. No./ID: 51,604), and PCR amplification is conducted with barcode-specific bacterial primers targeting the variable regions V3-V4 of the 16S rRNA gene: the forward primer 341F for 5′-CCTAYGGGRBGCASCAG-3’ and 806R for 5′-GGACTACNNGGGTATCTAAT-3’ [34]. Sequencing libraries and paired-end reads are generated on an Illumina HiSeq 2500 platform from Biomarker Technologies Co.Ltd. (Beijing, China) according to a standard protocol.

*ARGs detected by qPCR*

We then use quantitative PCR (*qPCR*) to detect the expression of ARGs in faecal samples. After a careful literature review, we selected 6 ARGs of four kinds of antibiotics: beta-lactam, tetracycline, fluoroquinolone, and macrolide, which are commonly used during pregnancy and early life [12, 35, 36]. Each sample includes three replicates for data accuracy.

**Table 1 Tab1:** Faecal sample collection at every timepoint of the Pregnancy and Birth Cohort in Northwest China (PBCC)

Stage	Timepoints	Period	Faecal sample	Sample source
Pregnancy	T1	1^st^ trimester	√	
	T2	2^nd^ trimester	√	Mother
	T3	3^rd^ trimester	√	
Delivery	T4	Birth	√	Infant
After birth	T5	42 days	√	
	T6	3 months	√	
	T7	6 months	√	Infant
	T8	12 months	√	
	T9	18 months	√	
	T10	24 months	√	

